### Sample size calculation

In order to detect a 5 mmHg between-group differences in postpartum blood pressure and in breastfeeding rates, we are aiming to recruit an approximate of 323 participants (after accounting for a 30% loss to follow-up). Around 278 of these participants (86%) will be randomized to either the breastfeeding intervention group or breastfeeding control group, and 45 participants (14%) who will not be breastfeeding will serve as a comparison group in the observational arm of the study. Accounting for annual delivery rates at each of the study sites and assuming that ~ 8% of deliveries are affected by HDP at all sites, and 70% of those will initiate breastfeeding (an average of general Canadian population initiation rate of ~ 90%, German HDP population rate of 40%, and United States rate of 82% in those with HDP) [48, 94] we anticipated reaching our recruitment target over a two-year period, without accounting for additional recruitment delays due to the pandemic.

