While few studies have specifically examined the relation between breastfeeding and postpartum BP after HDP, available evidence suggests a possible robust effect. A US study of 246 individuals with early or late-onset HDP who were 4 to 6 weeks postpartum found a mean decrease of 5.3 mmHg systolic (*p* = .03) and 3.6 mmHg diastolic BP (*p* = .04) among those who were lactating (*N* = 78) compared to non-lactating (*N* = 69) [32]. Another US study of 379 individuals with HDP demonstrated a mean decrease of 16.3 mmHg systolic/16.8 mmHg diastolic BP among those with gestational hypertension who breastfed for more than 6 months compared to no breastfeeding, adjusting for pre-pregnancy body mass index and other factors [33]. A Canadian cross-sectional analysis of postpartum BP and metabolic markers in 622 individuals with HDP and other pregnancy complications similarly found an 11% reduction in metabolic markers and a 6 mmHg decrease in median systolic BP among those who breastfed for more than 6 months compared to no breastfeeding, after adjusting for potential confounders [34]. While these observations warrant replication, the BP reductions associated with lactation exceed those seen with either weight loss [35] or antihypertensive pharmacotherapy [36].

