**Fig. 2 Fig2:**
[figure not shown]
Elevated Blood Pressure or Use of Anti Hypertensive Medication in Post Partum Women with HDP. This figure shows mean participant blood pressures according to study allocation group (breast feeding self-efficacy based intervention or usual postpartum care) at each of the study time points from the feasibility study “Breastfeeding and Blood pressure patterns in MOthers with hypertensive coMplications of pregnancy (BP-MOM)”. Elevated blood pressure was defined as average automated office blood pressure > 140/90 mmHg or average home blood pressure > 135/85 mmHg

In addition, mean breastfeeding self-efficacy scores (out of a total of 70) were higher in the intervention compared to the control group at 6 weeks (54.7 +/− 9.5 vs. 46.1 *+/−* 13.1), 3 months (55.3 +/− 13.9 vs. 46.3 +/− 15.9) and 6 months (57.2+/− 12.9 vs. 50.3 +/− 18.3). Compared with participants in the usual care group, those who received the BSEI were more likely to be breastfeeding exclusively at 6 weeks (71.4% vs. 44.4%) and 3 months (72% vs. 37%), and to continue breastfeeding to at least 6 months (90% vs. 58%).

The vast majority of participants assigned to the intervention group reported good or very good overall satisfaction with the BSEI at both 3 months (95%, *N* = 19) and 6 months (94%, *N* = 17). Given the positive outcomes and high acceptability of the BSEI, a recruitment rate of 50% within a high-risk obstetrical population, and participant retention of 82% at 6 months, our research team’s steering committee agreed that proceeding with a larger trial was warranted with a protocol adapted for COVID-19 pandemic contingencies (e.g., incorporating options for remote recruitment and measurements).

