### sheMATTERS trial hypotheses

The primary study hypotheses are that 1) individuals with HDP who receive the BSEI will have lower BP (approximately 5 mmHg systolic and/or 2 mmHg diastolic) compared to those who do not breastfeed, and 2) individuals with HDP who receive the BSEI will have a lower demand for antihypertensive treatment at 12 months postpartum compared with those who receive usual postpartum care. The secondary hypotheses are that:there will be a modest (10–20%) relative benefit in breastfeeding outcomes among participants with HDP who receive the BSEI compared to those who receive usual postpartum care;there will be a lower rate of metabolic syndrome in participants with HDP who receive the BSEI compared to those who receive usual postpartum care, and a greater difference when compared to those who do not breastfeed;rates of breastfeeding duration and exclusivity will be correlated with a greater tendency towards more cardioprotective behaviors over 12 months postpartum;infant neurodevelopment will be positively correlated with longer duration of any breastfeeding;severity of HDP, obesity, markers of inflammation, as well as education level and psychological symptoms at birth will be correlated with breastfeeding duration and exclusivity over 12 months postpartum.

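### The sample-size statement claims the trial can detect differences in breastfeeding rates, but its own 10–20% hypothesis has about 8–39% power, and the 5 mmHg effect is hypothesised against a different comparator from the one tested

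*Protocol article*

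**What the plan says.** All references are to the protocol article.

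- **Sample size calculation.** The purpose is given as "In order to detect a 5 mmHg between-group differences in postpartum blood pressure and in breastfeeding rates". The section continues: "we are aiming to recruit an approximate of 323 participants", a figure reached "after accounting for a 30% loss to follow-up". The total is split: "Around 278 of these participants (86%) will be randomized", and "45 participants (14%) who will not be breastfeeding will serve as a comparison group". The section does not name the groups behind the 5 mmHg, does not say whether it is systolic or diastolic, and gives no size for the breastfeeding difference.
- **sheMATTERS trial hypotheses.** The first primary hypothesis is about 5 mmHg lower systolic and/or 2 mmHg lower diastolic pressure with the intervention, measured against women who do not breastfeed. The first secondary hypothesis, against usual care, is "a modest (10–20%) relative benefit in breastfeeding outcomes".
- **Study objectives and Statistical analysis.** The primary question is whether the intervention lowers 12-month blood pressure or the need for antihypertensive therapy. The primary outcome is compared between the intervention and control groups by intention to treat.
- **Supportive pilot data.** Pilot usual-care rates were 58% for any breastfeeding to 6 months (intervention 90%), 37% for exclusive breastfeeding at 3 months (intervention 72%) and 44.4% for exclusive breastfeeding at 6 weeks (intervention 71.4%). The overall 12-month SDs were 13 mmHg systolic and 9.6 mmHg diastolic.

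**The concern.** A sizing statement tells readers what a null result means. This one says the trial can detect differences in breastfeeding rates, so a non-significant breastfeeding result would be read as evidence against the intervention. If the hypothesised benefit is far below what the sample can show, that reading is wrong.

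The blood-pressure part has a different problem. The stated effect is hypothesised against the non-breastfeeding women, who form a non-randomised group of 45. The primary analysis is between two randomised arms whose members have all started breastfeeding. The sizing section does not say which contrast its 5 mmHg refers to, so readers cannot tell what the trial was sized for.

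**Working it through.** **Inputs from the article:** 278 randomised 1:1; 30% loss; 45 non-breastfeeding women; the effects, pilot rates and pilot SDs above.

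**Assumptions, because the article does not state them:** two-sided alpha 0.05 (in line with its 95% confidence intervals); 80% power as the benchmark; pilot SDs and rates as planning values; 30% loss in the non-breastfeeding group too. All power figures use the normal approximation.

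**Step 1. The stated number.** n per arm = 2 × (1.96 + 0.84)² × SD² / difference². With SD 13 and difference 5 this is 106.1, rounded up to 107 per arm, or 214 in total. Multiplying by 1.3 gives 278.2, which matches 278. Dividing by 0.7, which is what leaves 214 after 30% loss, gives 306. Other SD and power pairs also fit 278, so its origin is inferred, not shown.

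**Step 2. Evaluable numbers.** 278 × 0.7 = 194.6, or 97.3 per arm. 45 × 0.7 = 31.5 non-breastfeeding women.

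**Step 3. Power for breastfeeding.** Power = Φ[(p2 − p1 − 1.96 × SE0) / SE1], with SE0 from the pooled proportion and SE1 from the separate ones. For 58% against 69.6%: SE0 = 0.0689, SE1 = 0.0684, so (0.116 − 0.1350) / 0.0684 = −0.28 and power is 39%.

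| Pilot control rate | 10% relative | 20% relative |
|---|---|---|
| 58% (any, 6 months) | 13% | 39% |
| 44.4% (exclusive, 6 weeks) | 9% | 23% |
| 37% (exclusive, 3 months) | 8% | 18% |

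With no loss at all (139 per arm), the 58% row becomes 17% and 52%. For 80% power, a 20% relative rise from 58% needs 269 per arm, and 2 × 269 / 0.7 is about 769 randomised. The pilot's own differences (58% vs 90%, 37% vs 72%) would have over 99% power.

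**Step 4. Power for blood pressure.** Power = Φ(difference / SE − 1.96), SE = SD × √(1/n1 + 1/n2).

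- Randomised arms, systolic: SE = 13 × √(2/97.3) = 1.864; 5 / 1.864 = 2.68; power 76%. The pilot arm SDs of 15.3 and 10.1 give 63% and 93%. Power reaches 80% at an SD of about 12.4.
- Randomised arms, diastolic 2 mmHg: SE = 9.6 × √(2/97.3) = 1.376; 2 / 1.376 = 1.45; power about 30%. SDs of 10.2 and 8.4 give 28% and 38%.
- Intervention arm against non-breastfeeding women, systolic: SE = 13 × √(1/97.3 + 1/31.5) = 2.665; power 47%.
- The same contrast, diastolic: SE = 9.6 × √(1/97.3 + 1/31.5) = 1.968; power 17%.

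**Step 5. What 97.3 per arm can detect with 80% power.** Systolic: 2.80 × 1.864 = 5.2 mmHg. Diastolic: 2.80 × 1.376 = 3.9 mmHg. Any breastfeeding from 58%: about 18.7 percentage points, to about 77%. That is 18.7 / 58 = 32% relative, against a hypothesised 10–20%.

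**The case against.** The strongest reply is that breastfeeding is a secondary hypothesis, that the sizing section attaches no size to it, and that the sample easily detects a difference as large as the pilot's. Breastfeeding outcomes also include durations in weeks and a time-to-event analysis, which power for a proportion does not cover. Much of this is fair. But the sizing sentence itself names breastfeeding rates, and the effect the article commits to is 10–20% relative, not the pilot's 32 points.

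On blood pressure, 76% is close to 80%. The pilot SD comes from 13 and 16 women with mixed home and office readings, and the 3- and 6-month SDs (12.1 and 11) were smaller. The wording "and/or" does not require separate power for diastolic pressure. Alpha, power and SD may be in the full protocol, so their absence here is not a fault. The 278/45 split is openly stated. All of this stands, and it limits the systolic shortfall to a small and uncertain one.

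Three stronger readings are tempting, and the article does not support them:

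- **That 5 mmHg was never meant for the randomised arms.** The sizing section names no groups, the primary analysis is between those arms, and 214 × 1.3 = 278 fits a two-arm calculation. What is shown is a conflict between sections.
- **That the true between-arm effect must be well under 5 mmHg.** A reader might multiply observational contrasts, such as a "6 mmHg decrease in median systolic BP among those who breastfed for more than 6 months compared to no breastfeeding", by the expected change in breastfeeding. That is an outside model. It ignores changes in duration and exclusivity and the other behavioural routes the article names. The pilot's 2 mmHg difference is too imprecise to settle it.
- **That breastfeeding power falls to about 5%.** That needs a control rate near 20%, which appears nowhere. The article gives no 6-month exclusive rate.

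**Conclusion.** The point holds in two parts.

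First, the claim that recruitment is sized for breastfeeding rates is wrong as written. The article's own hypothesis has about 8–39% power at 97 evaluable women per arm. Only a much larger difference, about 19 points from 58%, reaches 80%.

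Second, the blood-pressure effect is hypothesised against one comparator and tested against another, and the sizing section does not resolve this. At pilot SDs neither contrast reaches 80% power for the stated effects. Between the randomised arms the systolic shortfall is modest (76%) and disappears if the SD is about 12.4 or less. Diastolic power is low against either comparator.

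These figures rest on two-sided 0.05, an 80% benchmark, and pilot SDs and rates that the article does not declare as planning inputs. The breastfeeding conclusion is the firmer one, because it holds at every documented control rate and, at the most favourable of them, even with no loss to follow-up.

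**What to change.** 1. In the sample-size section, remove breastfeeding rates from the sizing claim, or replace them with the detectable difference: about 19 percentage points in any breastfeeding at 6 months, from an assumed 58%.
2. Base the statement on the 278 randomised women, not on 323. Possible wording: 278 randomised, about 195 evaluable after 30% loss, give 80% power at two-sided 0.05 for about 5.2 mmHg systolic (SD 13) and 3.9 mmHg diastolic (SD 9.6). Label the SDs, base rate, power and alpha as pilot-based assumptions, or replace them with the sponsor's own planning values and recompute.
3. Reconcile the comparator for the 5 and 2 mmHg effects across the hypotheses, objectives, sample-size and analysis sections. If 5 mmHg is meant as a difference between the randomised arms, say so and justify it for two arms that both start breastfeeding.

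The cost is text only. No extra recruitment is proposed, but the stated figures become less favourable.

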### Statistical analysis

Descriptive statistics will be used to characterize the study population. We will compare baseline characteristics in the experimental study arms to assess randomization effectiveness. We will assume two-sample tests such as chi-square tests, t-tests, and non-parametric tests as appropriate to assess between-group differences in various characteristics and outcome measurements. They include proportion on antihypertensive drug therapy, proportion of EBF at 6 months, total breastfeeding duration in weeks, total EBF in weeks, metabolic syndrome, as well as differences in physical activity and dietary patterns. Differences in the primary outcome between the intervention and control groups on study outcomes will be assessed using an intent-to-treat approach. To examine the effect of BSEI on systolic and/or diastolic BP at 12 months, we will use generalized linear regression (GLM) to model for continuous BP readings and the Generalized Estimating Equation (GEE) analyses using logistic regression (reduction of 5 mm in SBP from the baseline vs. no change). We will calculate beta estimates with 95% confidence intervals (CIs) after adjusting for any observed between group differences despite randomization. Given that we plan to recruit non-breastfeeding parents (*N* = 45), we will model breastfeeding first as a continuous exposure variable (number of weeks) with systolic BP as the outcome in a multivariable linear regression model. We will also evaluate the dose-response of breastfeeding categories (i.e., none, < 3 months, < 6 months, > 6 months) to determine systolic and diastolic BP trajectories. In a sensitivity analysis, we will use different combinations of systolic blood pressure and diastolic blood pressure, and delta change in BP from baseline will be assessed. Breastfeeding duration will be divided into quintiles/quartiles, and those will be correlated with a series of BP measures. We will also perform a survival analysis modeling time to cessation of exclusive breastfeeding in both study groups. The model will incorporate interval censoring and compare differences between groups controlling for variables of interest, such as baseline self-efficacy score, maternal education, income, and age. Kaplan-Meir curves and cox-regression will be used to address these aspects.

For secondary analyses, the statistical method to compare groups will depend on the distribution of the outcome variables in question. Mediation effects will be assessed using stratified analyses according to pre-defined clinically relevant characteristics such as parity (1 vs. > 1) and gestational age at delivery (34–37 weeks vs. > 37 weeks). Site-specific, sub-group analyses will be performed to know whether there are differences in the study populations. Statistical analysis will be performed using SAS 9.4 version, performed by the biostatistical unit at the primary study site, guided and overseen by the principal investigators.

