**Methods:**

We designed an open-label, multi-center 1:1 randomized behavioral trial to test whether a previously validated self-efficacy enhancing breastfeeding intervention can improve breastfeeding duration and/or exclusivity, and lower postpartum blood pressure at 12 months. Randomization is computer-generated and stratified by site (four hospitals in Montreal, Quebec and one hospital in Kingston, Ontario; all in Canada). Included are breastfeeding participants with HDP (chronic/gestational hypertension or preeclampsia) who delivered a live singleton infant at > 34 weeks, speak English or French, and have no contraindications to breastfeeding. Informed and written consent is obtained at hospitalization for delivery or a re-admission with hypertension within 1 week of discharge. Participants assigned to the intervention group receive a breastfeeding self-efficacy-based intervention delivered by a trained lactation consultant in hospital, with continued reactive/proactive support by phone or text message for up to 6 months postpartum. Regardless of group assignment, participants are followed for self-reported outcomes, automated office blood pressure, and home blood pressure at several time points with end of follow-up at 12 months.

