### Study outcomes

Our primary study endpoint is average systolic and/or diastolic BP, in mmHg, measured by standard recommended technique using validated automated office blood pressure devices. In the case of home blood pressure, an average of four daily measurements over a one-week period is used, after discarding the first day of measurement. Blood pressure data is collected at baseline, 6 weeks, 3 months, 6 months, and 12 months postpartum with the primary outcome at 12 months with repeat blood pressure and other cardiometabolic markers, as well as novel biomarkers. The purpose of the latter measurement is a secondary aim of sheMATTERS, which is enhanced cardiovascular phenotyping of those with HDP.

Our secondary study endpoint includes 1) elevated blood pressure (displayed automated mean blood pressure > 135 mmHg systolic and/or > 85 mmHg diastolic) or use of/increase in previous use of antihypertensive drug therapy, and 2) the presence of metabolic syndrome [83]. An additional secondary endpoint is systolic and/or diastolic blood pressure at 6months postpartum.

Breastfeeding outcomes include the duration of exclusive breastfeeding (in weeks), total breastfeeding duration (in weeks), the proportion of participants exclusively breastfeeding at 6 months, and the proportion of participants continuing any breastfeeding at 6 months and 12 months. Given high rates of in-hospital formula supplementation of breastfeeding infants born to persons with HDP [50], we have defined exclusive breastfeeding as the provision of nothing but breastmilk (either at the breast or via milk expression) after the first 7 days of life.

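### Total breastfeeding duration is assigned to ordinary two-sample tests with no handling of women lost while still breastfeeding; only exclusive breastfeeding gets a censoring-aware analysis

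*Protocol article*

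**What the plan says.** In the protocol article, Study outcomes names "total breastfeeding duration (in weeks") as a breastfeeding outcome, next to exclusive duration and "the proportion of participants continuing any breastfeeding at 6 months and 12 months".

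Statistical analysis then says: "We will assume two-sample tests such as chi-square tests, t-tests, and non-parametric tests as appropriate to assess between-group differences". The outcomes it lists for those tests include "proportion of EBF at 6 months, total breastfeeding duration in weeks, total EBF in weeks, metabolic syndrome".

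The same section adds: "We will also perform a survival analysis modeling time to cessation of exclusive breastfeeding in both study groups". That model is to allow for interval censoring and to use Kaplan-Meier curves and Cox regression. No matching analysis is planned for the end of any breastfeeding.

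The abstract describes measurement "with end of follow-up at 12 months". Sample size calculation allows for 30% loss to follow-up. Safety reporting says that a new pregnancy ends active follow-up. Participants and recruitment says that data from women who withdraw or are stopped by the team will be kept but left out of the analysis. For women who are simply lost, or who are still breastfeeding at month 12, nothing says what value enters the total-duration comparison.

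**The concern.** A t-test or ordinary rank test needs a completed duration for every woman. Two groups will not have one:

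- **Still breastfeeding at 12 months.** The plan expects such women, since breastfeeding at 12 months is itself an outcome. Their value is known only to exceed 52 weeks. If the intervention works, more of them are in the intervention arm.
- **Lost earlier while breastfeeding.** Their value is known only to exceed the last week of contact, and that week differs from woman to woman.

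The analyst must then score these women at their last known week, drop them, or keep only women with an observed stop. Each choice gives a different difference and different power, and the plan does not choose. Exclusive breastfeeding has a planned model that accommodates censoring. Any-breastfeeding duration lasts at least as long and is more exposed to both problems, yet it has none.

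**Working it through.** The protocol gives no figure for total duration, so there is nothing to reproduce. The size is illustrated from its other figures.

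**Inputs from the document**
- Pilot breastfeeding to at least 6 months: 90% intervention, 58% usual care (Supportive pilot data).
- Hypothesised relative benefit in breastfeeding outcomes: 10–20% (trial hypotheses).
- Randomised: 278 at 1:1, so 278 / 2 = 139 per arm.
- Loss to follow-up: 30%. Follow-up: 12 months, taken as 52 weeks.

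**Assumptions not in the document**
- Constant weaning rate, with control anchored at 58% at week 26.
- Benefit of 15%, the middle of the stated range: 0.58 × 1.15 = 0.667 at week 26.
- 30% of women lost, evenly over weeks 0–52. As a rough check, this implies 15% lost by 6 months; the pilot lost 1 − 37/45 = 18% by then.
- Exact stop weeks known, and loss unrelated to weaning.

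**Step 1. Share still breastfeeding at week 52.** With a constant rate, S(52) = S(26)².
- Control: 0.58² = 0.34. Intervention: 0.667² = 0.44.
- With Weibull shapes 0.7 to 2 and a 10–20% benefit, the ranges are 11–41% in control and 17–56% in intervention. The share is higher in the better arm in every scenario.

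**Step 2. Mean weeks up to 52, nobody lost.** Rate λ = −ln S(26) / 26; mean to week 52, M = (1 − S(52)) / λ.
- Control: 1/λ = 47.7, M = 47.7 × (1 − 0.336) = 31.7 weeks.
- Intervention: 1/λ = 64.2, M = 64.2 × (1 − 0.445) = 35.6 weeks.
- Difference: 4.0 weeks (3.97 before rounding the arms).

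**Step 3. Lost women scored at last known week.** For a woman lost at a uniformly distributed week, the mean recorded duration is (1/λ) × (1 − M/52).
- Control: 47.7 × (1 − 31.7/52) = 18.7. Intervention: 64.2 × (1 − 35.6/52) = 20.2. Difference about 1.5.
- Mixture: 0.7 × 3.97 + 0.3 × 1.5 = 3.2 weeks, against 4.0.

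**Step 4. Power by simulation, 139 per arm, two-sided 5%**

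| Situation (15% benefit) | Power |
|---|---|
| Nobody lost: t-test / rank test / log-rank | about 43% / 47% / 50% |
| 30% lost: t-test on last known week | about 30% |
| 30% lost: t-test with lost women dropped | about 32% (difference stays 4.0 weeks) |
| 30% lost: t-test on observed stops only | about 8% |
| 30% lost: log-rank with censoring | about 44% |

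At a 20% benefit with 30% lost, the t-test on last known week has about 49% and the log-rank about 67%. With loss at a constant rate instead of evenly, a 20% benefit gives 48% (last known week), 9% (observed stops only) and 67% (log-rank); a 10% benefit gives 17%, 7% and 21%. Under that loss pattern, the observed-stops difference is only 0.8 weeks at a 10% benefit and 1.4 weeks at 20%.

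**Step 5. No effect.** Rejection stays at about 4–5% for all methods.

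**The case against.** The best case for the plan has four parts.

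1. **The list of tests is open.** It says non-parametric tests as appropriate, and the section lets the method for secondary analyses follow the outcome's distribution. Log-rank and Gehan-Wilcoxon are non-parametric two-sample tests that handle censoring, so the wording does not force a t-test on incomplete values. This stands in part. But the section names survival methods where it wants them, and does so for exclusive breastfeeding only.
2. **The 12-month cut does little damage.** This stands. With nobody lost, the rank test trails the log-rank by about 3 points. A t-test on durations capped at 52 weeks validly estimates mean weeks up to 12 months, and the breastfeeding objectives and hypotheses are already framed over 12 months.
3. **The outcome is not central.** This stands. It is one of several breastfeeding outcomes, none primary, and the 6- and 12-month proportions are not distorted by the cut.
4. **An analysis plan not shown may settle censoring.** It may. The point here is that the protocol assigns this outcome a class of test that, in its ordinary form, does not fit.

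A reader might infer more: that the trial would understate a true gain of 16.5 weeks (64.2 − 47.7) as 4.0. The documents do not support that. The 16.5 extends a constant weaning rate indefinitely past week 52 from one pilot percentage; across curve shapes and a 10–20% benefit, the share of the uncapped difference retained runs from 9% to 73%. No analysis of 12-month data would estimate that quantity.

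**Conclusion.** The concern holds in limited form. The protocol gives total breastfeeding duration a method that, as ordinarily applied, has no place for women lost while breastfeeding, and restricts its censoring-aware analysis to exclusive breastfeeding. The 12-month cut chiefly makes the estimand mean weeks up to week 52. The real cost comes with early loss: at a 15% benefit, a difference of 3.2 instead of 4.0 weeks and about 30% instead of 44% power if last known weeks are used, and almost no power if only observed stops count.

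These sizes rest on the assumed weaning curve and loss pattern. The protocol gives neither the 12-month breastfeeding rate nor the timing of loss. A reader might also infer a risk of false-positive results, or a threat to the primary outcome. Neither follows: type I error holds, and the blood pressure comparison is untouched. Nor is exclusive breastfeeding left without a suitable method. The change is worth making because it is cheap and improves a stated method.

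**What to change.** - In Study outcomes, define the outcome as duration of any breastfeeding up to 12 months.
- In Statistical analysis, take it out of the two-sample-test list and extend the planned survival analysis (interval censoring, Kaplan-Meier, Cox) to time to cessation of any breastfeeding by randomised arm. Censor women still breastfeeding at 12 months, or lost, at their last known breastfeeding date. Report the hazard ratio with the restricted mean weeks to 52.
- For exclusive breastfeeding, name the survival analysis already planned as the between-arm comparison of duration.
- Reconcile this with the statement in Participants and recruitment that data from withdrawn or stopped women are not analysed; censoring those women needs their earlier data.

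The cost is a few sentences. No new data are needed, since the Infant Feeding Questionnaire already collects duration until cessation is reported. The downside is small: the estimate covers only the first 12 months and relies on loss being non-informative.
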